# Efficacy and cost-utility of the eHealth self-management application 'Oncokompas', helping partners of patients with incurable cancer to identify their unmet supportive care needs and to take actions to meet their needs: a study protocol of a randomized controlled trial

**DOI:** 10.1186/s13063-019-4037-5

**Published:** 2020-01-31

**Keywords:** Incurable cancer, Caregiving, Partners, eHealth, Self-management, Caregiver burden

## Abstract

**Background:**

Incurable cancer does not only affect patients, it also affects the lives of their partners. Many partners take on caregiving responsibilities. The burden of these caregiving tasks are often associated with physical, psychological, and social difficulties and many partners have unmet supportive care needs. Oncokompas is an eHealth self-management application to support partners in finding and obtaining optimal supportive care, tailored to their quality of life and personal preferences. A randomized controlled trial will be carried out to determine the efficacy and cost-utility of Oncokompas.

**Methods:**

A total of 136 adult partners of patients with incurable cancer will be included. Partners will be randomly assigned to the intervention group, which directly gets access to Oncokompas, or the waiting-list control group, which gets access to Oncokompas after three months. The primary outcome measure is caregiver burden. Secondary outcome measures comprise self-efficacy, health-related quality of life, and costs. Measures will be assessed at baseline, two weeks after randomization, and three months after the baseline measurement.

**Discussion:**

This study will result in evidence on the efficacy and cost-utility of Oncokompas among partners of patients with incurable cancer, which might lead to implementation of Oncokompas as a health service for partners of patients with incurable cancer.

**Trial registration:**

Netherlands Trial Register, NTR 7636. Registered on 23 November 2018.

## Background

It is well known that cancer does not only affect patients; the disease also has a considerable impact on the lives of their partners [1, 2]. Partners of patients with incurable cancer often help with personal care and provide practical and emotional support to patients [3, 4]. It is not uncommon that they perform caregiving tasks they are not trained for (e.g. the management of medication and symptoms). Partners may feel overwhelmed by these tasks. They often also consider their own problems as less important than those of the patient [5, 6]. Since cancer increasingly becomes a chronic illness, partners of patients with cancer are challenged to be involved in the management of the patient’s care and quality of life for an increasing extent of time, while also maintaining their own wellbeing [7].

Although caring for a loved one can be rewarding [8], informal caregiving responsibilities are also associated with physical, psychological, and social difficulties [1, 4, 9–11]. Frequently reported symptoms among caregivers are sleeping problems, fatigue, and psychological distress [12–14]. Many partners have to give up (part of) their normal daily activities due to their caregiving tasks, for example their work or social activities [1, 15]. Partners may experience high burden levels related to their responsibilities and the impact of the caregiving on their daily lives [1, 5, 16]. Caregiver burden is defined as “the extent to which caregivers perceive that caregiving has an adverse effect on their emotional, social, financial, physical, and spiritual functioning” [17]. Studies have shown that these adverse effects negatively influence the quality of life of partners [1, 2, 9–14, 18–20].

Many partners do not know where to go for advice and guidance or do not have time to seek help [13, 21–23]. Therefore, there is a growing interest in self-management interventions and eHealth applications as ways to improve (the early access to) supportive care targeting partners of patients with incurable cancer [7, 24, 25].

The eHealth self-management application Oncokompas has been developed to support patients and partners of patients with incurable cancer in finding and obtaining optimal supportive care. Oncokompas helps them to monitor their quality of life using patient-reported outcome measures (PROMs), followed by automatically generated tailored feedback, self-care advice, and advice on supportive care services. The content of the version of Oncokompas for partners is focused on self-care of the partner and targets the partner alone instead of the couple (i.e. patient and partner together), for example to inform and advise partners about their shifting roles and responsibilities, their relationship, financial resources, and their work situation. The application is tailored to the partner’s health status and personal preferences. There is a dedicated version of Oncokompas available for patients treated with curative intent [26–28] and for patients with incurable cancer [29]. The aim of this randomized controlled trial (RCT) is to determine the efficacy of Oncokompas as a self-management instrument on caregiver burden, general self-efficacy, and health-related quality of life among partners of patients with incurable cancer and to assess its cost-utility.

## Methods/Design

### Study design

A prospective RCT with two parallel groups will be conducted to determine the efficacy and cost-utility of Oncokompas among partners of patients with incurable cancer.

Partners will be randomly assigned to the intervention group or the waiting-list control group. Partners in the intervention group will get direct access to Oncokompas, while partners in the control group will get access to the intervention three months after the baseline measurement (i.e. after completion of the last questionnaire). Partners will receive three questionnaires: at the time of inclusion (t0), two weeks after randomization (t1), and three months after the baseline measurement (t2). Figure 1 shows the flow diagram of the RCT. Figure 2 shows the schedule of enrollment, intervention, and assessments (according to the Standard Protocol Items: Recommendations for Intervention Trials (SPIRIT), see Additional file 1).

**Fig. 1 Fig1:**
[figure not shown]
Flow diagram of the randomized controlled trial

**Fig. 2 Fig2:**
[figure not shown]
The schedule of enrollment, intervention, and assessments of the randomized controlled trial (according to SPIRIT)

This study is approved by the VUmc Medical Ethical Committee (registration number 2018.517). All respondents will provide written informed consent before inclusion and will be informed that participation is voluntary. Partners can withdraw from the study at any time without any consequences.

### Study population

#### Inclusion and exclusion criteria

In this study, partners of patients with incurable cancer will be included. Partners are included when they are aged ≥ 18 years and have access to an e-mail address. Partners are excluded when they have severe cognitive impairments or psychotic behavior, or when they have a poor understanding of the Dutch language (and thereby are not able to complete a questionnaire in Dutch). They will also be excluded when they already used Oncokompas earlier in life (e.g. if they have had cancer themselves) or when their partner with cancer participates in the Oncokompas RCT, which is currently conducted among patients with incurable cancer [29].

### Study procedures

In this study, a multi-component recruitment strategy is followed. Partners will be recruited through: (1) (online) recruitment materials, (2) healthcare professionals, and 3) direct contact with the researcher. Table 1 gives an overview of the different recruitment strategies used within this study.

**Table 1 Tab1:** Overview of the different recruitment strategies

Recruitment strategy	Recruitment channel
Recruitment through (online) recruitment materials	Online: • Online advertising on websites and online newsletters • Social Printed: • Advertisements in newspapers and magazines • Leaflets and posters in offices of healthcare professionals Recruitment through: • Relevant organizations targeting informal caregivers or relatives of (cancer) patients • Cancer patient organizations • Walk-in consultation services • Hospitals • Psycho-oncological care centers
Recruitment through a healthcare professional	• Healthcare professionals (e.g. psychologists, rehabilitation centers, general practitioners, physiotherapists, nurse practitioners)
Recruitment through face-to-face contact with the researcher	• Events targeting partners of patients with incurable cancer

#### Recruitment through (online) recruitment materials

Several recruitment materials have been developed to recruit partners through online channels. The contact details of the researcher and URL of the website of Oncokompas (www.oncokompas.nl) are mentioned in all recruitment materials. On the Oncokompas website, partners can find more information about Oncokompas and the study, such as how they can apply to participate. When partners are interested in participating in the study, they can fill in an online contact form on the website.

#### Recruitment through a healthcare professional

Partners eligible to participate will also be approached through healthcare professionals. When a partner is interested in participating in the study, the researcher will contact the partner by phone to further inform him or her about the study.

#### Recruitment through direct contact with the researcher

Partners will also be informed about the study on events targeting relatives of patients with incurable cancer. If interested, they will receive an information letter about the study.

To summarize, many organizations throughout the Netherlands will be involved in the study by informing and referring partners of patients to the website of Oncokompas (or directly to the research team); all other actions regarding the study are carried out by the research team of the Vrije Universiteit Amsterdam, the Netherlands. Therefore this study is marked as a monocenter study.

#### Partners who want to participate

Partners meeting the inclusion and exclusion criteria will receive an information package by post (consisting of an information letter, an informed consent form, and a reply envelope). If partners want to participate in the study, they are asked to return the signed informed consent form using the reply envelope. After the coordinating researcher has received the signed informed consent form, this researcher will send partners a link to the online baseline questionnaire by e-mail. After completion of the first questionnaire, partners will be randomized into the intervention group or the control group. Partners randomized to the intervention group will receive an invitation e-mail for Oncokompas to activate their personal account. Partners randomized to the control group will receive an e-mail to activate their account after completion of the last questionnaire (t2).

#### Randomization

Randomization takes place in a 1:1 ratio. Block randomization will be used to randomly assign partners to the intervention group or the control group. Block size varies between 4–8. Random allocation software (i.e. Sealed Envelope) is used by a researcher not involved in the study to create the randomization scheme. This researcher also carries out the allocation process during the study and notifies the coordinating researcher of the study of the outcome of the allocation. The coordinating researcher will send partners the invitations to activate their Oncokompas account, which means that blinding of the researcher is not possible. Trial participants themselves are also aware of the outcome of the allocation; they receive an e-mail with the outcome of the allocation after they filled in the first questionnaire.

Neither the outcome assessors nor data analysts are blinded regarding the outcome of the allocation. The design of the study is open label; therefore unblinding will not occur. There will be no special criteria for discontinuing or modifying allocated interventions.

### Intervention

Oncokompas is an eHealth self-management application that supports people with cancer and their partners to adopt an active role in the management of their own wellbeing. It supports them in finding and obtaining optimal supportive care, tailored to their own health status, personal characteristics, and preferences. The content of Oncokompas is developed following a stepwise, iterative, and participatory approach, actively involving users and other stakeholders in the design process [30]. In the present study, the version of Oncokompas tailored to partners of patients with incurable cancer is used.

Oncokompas consists of three components: (1) Measure, (2) Learn, and (3) Act. After the log-in procedure, a user enters the first component of Oncokompas which starts with a general questionnaire. Based on this general questionnaire, Oncokompas makes a selection of the topics suitable for this particular user (e.g. when someone has no children, the topic about the relationship with children will not be shown). After this, the user can select which topics he or she wants to address in Oncokompas. The topics target different domains of quality of life; physical, psychological and social functioning, and existential issues. An overview of the topics covered in Oncokompas for partners is shown in Table 2. Subsequently, in the first component “Measure,” a user can complete PROMs on the chosen topics. The PROMs were selected based on Dutch practical guidelines and literature searches, in collaboration with a team of healthcare professionals, partners of patients with cancer, and patients with cancer. Algorithms were developed to link the scores on the PROMs to tailored feedback in the “Learn” component. The algorithms are based on available cut-off scores, Dutch practical guidelines, and/or consensus by teams of experts (i.e. healthcare professionals, partners, and patients).

**Table 2 Tab2:** Overview of all topics covered in Oncokompas for partners of incurably ill cancer patients

Domain	Topics
Physical	Fatigue Sexuality Sleep problems Shoulder and back pain Changed role of nutrition in the late palliative phase (topic to inform partners)
Psychological	Anxiety (as a result of the patient’s cancer) Coping with emotions Depression Nervousness
Social	Caregiver burden Choices concerning the end-of-life of the patient Loneliness Communication with the physician of the patient Social life Relationship with patient Relationship with children Work issues
Existential	Saying farewell

Then the user enters the “Learn” component, in which feedback on his or her outcomes is provided, tailored to his or her health status, characteristics, and preferences. First, a user gets an overview of his or her overall wellbeing on topic level. A three-color system is used to express the level of wellbeing. When a user is doing well on a topic, he or she gets a green score. An orange score means that a user could use attention and support on that topic. A red score indicates that a user may need professional care. Oncokompas also provides feedback on interrelated symptoms (e.g. caregiver burden and fatigue). The “Learn” component concludes with comprehensive self-care advice, such as tips and tools, tailored to the individual user.

The third step within Oncokompas is the “Act” component, in which users are provided with personalized supportive care options, tailored to their health status and preferences (e.g. preferences for individual therapy versus group therapy). When a user has a red score on a topic, the feedback always includes the advice to contact a healthcare professional, such as a general practitioner or a specialized healthcare professional (e.g. a psychologist) [26]. When a user has an orange score on a topic, the feedback includes suggestions for self-help interventions.

Oncokompas is meant as an additional form of support for partners of patients with incurable cancer. It is not meant as a replacement of a healthcare professional.

### Care as usual

In this study, care as usual is defined as the care provided by any healthcare professional and includes all medical and supportive care that partners of patients with incurable cancer would receive, regardless of their participation in this study.

### Outcome assessment

Caregiver burden is the primary outcome measure used to assess the efficacy of Oncokompas among partners of patients with incurable cancer. Secondary outcome measures are general self-efficacy and health-related quality of life. In addition, outcomes on cost-utility will be measured.

Measurements will be collected at baseline (t0), two weeks after randomization (t1), and three months after the baseline measurement (t2). Measurements will be assessed through online questionnaires. An overview of the primary and secondary outcome measures is shown in Table 3.

**Table 3 Tab3:** Measurement overview

Aim		Outcome measures	Instrument
Efficacy	Primary outcome measure Secondary outcome measures	Caregiver Burden Self-efficacy	Caregiver Strain Index + (CSI+) General Self-Efficacy Scale (GSE)
Cost-utility		Health-related quality of life Medical costs Productivity costs Costs of Informal Care	EuroQol 5 Dimensions (EQ-5D-5L) iMTA Medical Consumption Questionnaire (iMCQ) iMTA Productivity Cost Questionnaire (iPCQ) iMTA Valuation of Informal Care Questionnaire (iVICQ)

### Primary outcome measure

#### Caregiver strain index +

Caregiver burden is assessed with the Caregiver Strain Index + (CSI+). The CSI+ is an extended version of the Caregiver Strain Index, developed in 1983 [31]. The original 13-item CSI measures the burden that informal caregivers experience as a result of caring for their loved ones. In the CSI+ questionnaire, five positive items were added to the original CSI. These positive items fall into two categories: “coping” factors and “attitudinal” factors. All items of the CSI+ are completed with “yes” or “no” and are equally weighted to calculate a carer’s total CSI+ score. Research showed that the internal consistency (Cronbach’s alpha) for the 13-item CSI was 0.86 [31]. Furthermore, a study testing the feasibility and validity of the CSI+ reported that by including positive aspects of care, resulting in the CSI+, an improved convergent validity of the Caregiver Strain Index is realized [32].

### Secondary outcome measures

#### General self-efficacy scale

The General Self-Efficacy Scale (GSE) is a 10-item questionnaire, assessing how a person deals with difficult situations in his or her life. The items have a 4-point Likert scale, in the range of 1–4 (i.e. not at all true, hardly true, moderately true, and exactly true). The total score is in the range of 10–40 and is calculated by adding up the scores on the 10 items. A higher score indicates a greater generalized sense of self-efficacy [33]. A study examining the psychometric properties of the GSE showed that the GSE scale is reliable, homogeneous, and unidimensional [34].

### Cost-utility evaluation

To evaluate the cost-effectiveness of Oncokompas compared to current care, a cost-utility analysis will be conducted in which the difference in total three-months costs between the two study arms is compared to the difference in quality-adjusted life years (QALYs) based on the EuroQol 5 Dimensions.

#### Health-related quality of life

The EuroQol 5 Dimensions (EQ-5D-5L) will be used to measure health-related quality of life on five dimensions of health (i.e. mobility, self-care, usual activities, pain/discomfort, and anxiety/depression), presented to the respondent by five items which all have five answer categories (i.e. no problems, some problems, moderate problems, severe problems, and extreme problems/unable to). As a result, the EQ-5D-5L can describe 3125 unique health states. After completion of the questionnaire, the profile of answers can be transformed to a value given by the general public using the Dutch index tariff of the EQ-5D index [35]. The EQ-5D is a validated questionnaire to measure health-related quality of life [36, 37].

#### Medical consumption questionnaire, productivity cost questionnaire, and valuation of informal care questionnaire

To measure the costs of healthcare, the costs for patients and their families (e.g. travelling costs and help received from family and friends), and costs within other sectors (i.e. productivity losses from paid and unpaid work) in the previous three months, an adapted version of the medical consumption questionnaire (iMCQ) and productivity cost questionnaire (iPCQ) will be used. An adapted version of the valuation of informal care questionnaire (iVICQ) will be used for the valuation of informal care by monetary and non-monetary methods. All these questionnaires are developed by the Institute for Medical Technology Assessment of the Erasmus University Rotterdam (iMTA), the Netherlands [38–40].

#### Sociodemographic characteristics and health-related characteristics

A study-specific questionnaire will be used at baseline (t0) to assess the sociodemographic characteristics (e.g. age, education level, and work situation) and health-related characteristics of the partner as well as the health situation of the patient with cancer.

### Sample size

To demonstrate the presence of an effect on the CSI+ of at least 0.5 standard deviations as statistically significant in a one-tailed test at alpha = 0.05 and a power of (1 - beta) = 0.80, a minimum of 51 participants in each condition of the RCT will be required at follow-up. Anticipating a drop-out rate of 25% between t0 and t2, 68 participants per condition need to be included at t0. Therefore, the total study cohort comprises 136 partners of patients with incurable cancer.

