### Statistical analyses

All analyses will be conducted in agreement with the intention-to-treat principle. Descriptive statistics will be used to describe the sociodemographic characteristics, health-related characteristics of the partner, the health situation of the patient with cancer, and the outcome measures. Chi-square tests and independent samples t-tests will be used to analyze whether randomization resulted in a balanced distribution of sociodemographic and health-related characteristics across the study arms. Mann–Whitney U tests will be performed in case of non-normality of the data. To test whether there are differences in the outcomes across the study arms at baseline, independent samples t-tests will be used.

Linear mixed models (LMM) will be used to determine the efficacy of Oncokompas by comparing longitudinal changes between the intervention group and control group with fixed effects for study arm, time, and their two-way interaction, as well as a random intercept for individuals.

LMM will also be used to determine whether age, gender, socioeconomic status (e.g. education level and work situation), the health situation of the patient, and baseline quality of life moderate the efficacy of Oncokompas with fixed effects for study arm, time, the potential moderator, and all two-way and three-way interaction effects, as well as a random intercept for individuals.

Post-hoc analyses will be applied when significant results are found in the efficacy and moderation analyses. To measure the differences in change between the intervention group and control group at follow-up measurements, independent samples t-tests with Bonferroni correction will be used. These tests will also be used to assess whether change scores between the intervention group and control group differed significantly within each category of the significant moderator variables.

The effect sizes (ES) of the intervention will be measured by calculating the (between group) Cohen’s d. The magnitude of the ES is classified as large (≥ 0.80), moderate (0.50–0.79) or small (< 0.50) [41].

A *p* value < 0.05 will be considered significant for all analyses. All tests will be one-tailed. IBM Statistical Package for the Social Sciences (SPSS) version 26 (IBM Corp., Armonk, NY USA) will be used to perform all statistical analyses.

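### The 80% power is calculated for one one-sided t-test at one time point, not for the arm-by-time mixed model with gated, Bonferroni-corrected t-tests that the plan runs

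*Protocol article*

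**What the plan says.** The Sample size section of the protocol article aims to detect "an effect on the CSI+ of at least 0.5 standard deviations" "in a one-tailed test at alpha = 0.05 and a power of (1 - beta) = 0.80". From this it concludes that "a minimum of 51 participants in each condition of the RCT will be required at follow-up". It then allows for loss to follow-up: "Anticipating a drop-out rate of 25% between t0 and t2, 68 participants per condition need to be included at t0". The total is 136. The test, the correlation between visits and the scale of the effect (score or change) are not named.

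The Statistical analyses section determines efficacy with a linear mixed model "with fixed effects for study arm, time, and their two-way interaction, as well as a random intercept for individuals". There are three measurements: baseline (t0), two weeks (t1) and three months (t2). What follows is conditional: "Post-hoc analyses will be applied when significant results are found in the efficacy and moderation analyses". For between-arm differences in change at the follow-ups, "independent samples t-tests with Bonferroni correction will be used". The same section makes every test one-tailed with a 0.05 threshold. It does not state how time is coded or which follow-up is primary.

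**The concern.** The article fixes both the basis of the sample size and the sequence of tests, and the two do not match. The sample size assumes one comparison at one time point with the full one-sided 0.05. The analysis tests the interaction over both follow-ups, and any statement about a particular follow-up comes from a corrected t-test that is reached only through that interaction.

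The one-tailed rule adds a second inconsistency. With time categorical, the interaction test is a 2-df F test, which has no direction. The one-sided alpha behind the 51 is then not available for the test that decides efficacy.

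At stake is whether a true 0.5 SD reduction in caregiver burden at three months could be missed more often than the stated 20%.

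**Working it through.** **1. Reproducing the plan's figure.** Inputs from the Sample size section: d = 0.5, one-sided alpha 0.05, power 0.80. Allocation is equal ("Randomization takes place in a 1:1 ratio"). The power of a two-sample t-test follows from the noncentral t with 2n − 2 df and noncentrality d√(n/2).
- n = 50 per arm: 79.9%.
- n = 51 per arm: 80.6%.
- Drop-out: 51 / 0.75 = 68 per arm; 2 × 68 = 136.

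All three figures reproduce. No correlation, repeated measure or multiplicity allowance enters.

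**2. Assumptions for the planned analysis.** These are not in the documents: time is categorical; the correlation ρ is the same between all visits (as a random intercept implies) and ranges from 0.3 to 0.7; the effect is 0.5 SD at t2 and 0, 0.25 or 0.5 SD at t1; 51 per arm are complete; Bonferroni divides by two follow-ups, giving one-sided 0.025 each.

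**3. Interaction test (2 df).** The arm differences in change at t1 and t2, (a, b), have covariance V = (2/n)(1 − ρ)[[2, 1], [1, 2]]. With n = 51 the noncentrality is

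λ = 17(a² − ab + b²) / (1 − ρ).

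With b = 0.5:
- a = 0 or 0.5: λ = 4.25 / (1 − ρ), which is 8.5 at ρ = 0.5.
- a = 0.25: λ = 3.1875 / (1 − ρ), which is 6.4 at ρ = 0.5.

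Power is taken from the noncentral F with 2 and 200 df at 0.05. It is lowest when the t1 effect is half the t2 effect, so the lower end of each range is a worst case.

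**4. Interaction test and Bonferroni t-test at t2, both significant.** This was simulated with 20,000 runs per setting.

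**5. A single contrast of change at t2.** The standardised effect is 0.5/√(2(1 − ρ)): 0.423 at ρ = 0.3, 0.500 at 0.5, 0.559 at 0.6 and 0.645 at 0.7. Power is from the formula in step 1 at one-sided 0.05.

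| ρ | 2-df interaction alone | Interaction and Bonferroni t-test at t2 | Single t2 change contrast, one-sided 0.05 |
|---|---|---|---|
| 0.3 | 46–58% | 44–49% | 68% |
| 0.5 | 61–74% | 59–65% | 81% |
| 0.6 | 71–83% | 70–76% | 88% |
| 0.7 | 83–93% | 83–88% | 94% |

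**6. Partial data.** The mixed model also uses the earlier visits of the 17 drop-outs per arm (68 − 51). If 9 to 17 of them are seen at t1, the interaction test at ρ = 0.5 has about 64–84%, and the interaction plus the t2 t-test about 61–68%.

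**The case against.** Four points can be made for the plan.

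*Nothing is miscalculated.* This stands. The 51, 68 and 136 are right for the test they describe. The fault is that sizing and analysis are not aligned.

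*The Bonferroni t-tests are not a condition for efficacy.* This also stands. A reader might infer from the table that the plan delivers only 59–65% power. The article does not support that reading. It determines efficacy with the mixed model and calls the t-tests post hoc, and it nowhere requires a significant t-test at t2. The 59–65% is the joint chance of passing both steps at an assumed correlation of 0.5. It matters for a claim about burden at three months specifically, because a significant interaction gives neither direction nor time point.

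*The 2 df are inferred, and the one-tailed rule fits a 1-df contrast better.* This stands in part. Unevenly spaced visits and t-tests at the follow-ups point to categorical time, but the coding is not stated. If the intended test is a single t2 contrast, power at ρ = 0.5 is 81% and the stated 80% holds there. The article does not say that this is the test.

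*The time point is implied, and details may be in the full protocol.* Drop-out is counted to t2, so the 51 does refer to three months. But the gate and the correction are set out in the article itself and conflict with the sizing, so this is more than omitted detail.

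**Conclusion.** The point holds in this form: the stated 80% belongs to a test that the plan does not describe running, and the one-tailed rule cannot apply to a 2-df interaction test. With 51 completers per arm and categorical time, the interaction test alone falls below 80% across the t1 effects considered at correlations of 0.5 or lower, straddles 80% at 0.6 and exceeds it at 0.7. Counting partial data moves the figure at 0.5 to about 64–84%. It would go too far to call the trial underpowered outright: the documents give no correlation, and at about 0.7 even the full two-step chain has 83–88%.

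**What to change.** Name one primary test: the arm difference in CSI+ at t2 (three months), as a 1-df contrast from the mixed model, with its direction and alpha stated. Do not make it depend on the interaction test and do not Bonferroni-correct it. Make t1 secondary. Report the t2 estimate with its confidence interval whatever the p value.

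Base the stated power on that contrast with an explicit correlation. As a change contrast at one-sided 0.05 with 51 per arm, it is about 68% at ρ = 0.3, 81% at 0.5 and 94% at 0.7, and higher with baseline adjustment. It exceeds the two-step chain at each correlation in the table, partly because the whole one-sided 0.05 is spent at t2, as the sample size calculation already assumes.

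If the present chain is kept, replace the 80% with the power of that chain over a stated range of correlations, not a single figure, and drop the one-tailed rule for the interaction test.

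The change is to wording only and needs no extra participants. The cost is that t1 loses any co-primary role.
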